#### 2.6.4. Interventions for the Control Group

Participants randomised to the TAU control group will receive BUP/NX-F dosing according to preference of daily, twice weekly, or every two weeks alternatives without a mandatory supervised dosing period. In this group, take-home doses will be provided contingent on provision of negative UDS only without following a fixed protocol. Medication management sessions will not be delivered according to structured manual and no monitoring of BUP levels will be done.  Table 3 contrasts the interventions under the experimental and control group.

### 2.7. Study Outcomes

#### 2.7.1. Primary Outcome

The primary outcome measure for the study will be the count of negative opioid UDS (excluding BUP) over 16 weeks. Scheduled appointments for a UDS that are missed will be conservatively imputed as positive for opioids.

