**Methods:**

The Suboxone Treatment and Recovery Trial (STAR-T) is a single site, 16-week, parallel-group, randomised controlled trial. The aim of the study is to determine the effectiveness of a medication management framework including TDM and UDS to enable patients enrolled on outpatient OAT (with buprenorphine/naloxone [sublingual film formulation; BUP/NX-F; Suboxone™]) to receive stepped take-home doses. Following stabilisation during inpatient care, adult participants with illicit or prescription OUD were allocated (1:1) to receive (1) BUP/NX-F plus medication management for take-home doses based on TDM, UDS, and contingency management protocol (the experimental group) or (2) BUP/NX-F plus UDS only (treatment-as-usual, the control group). The primary outcome is the mean percentage of negative UDS over 16 weeks. The secondary outcome is treatment retention defined as completion of 16 weeks of OAT without interruption. There will be an exploratory analysis of the association between participant characteristics, clinical data, and outcomes.

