#### 2.4.1. Urine Drug Screen (with Confirmatory Testing; Baseline and Every Clinic Visit) and BUP Level Determination (See Section 2.7 for Frequency of Administration)

A 5-minute, point-of-care immunoassay UDS test will be used that is US FDA approved and Clinical Laboratory Improvement Amendments (CLIA) waived for the following drugs screen in urine: opioids (morphine for illicit heroin), propoxyphene, tramadol, oxycodone, benzodiazepines, tricyclic antidepressants, psychostimulants (d-amphetamine, methyl-amphetamine, MDMA, cocaine), cannabinoids, phencyclidine, and BUP. All urine samples were collected under supervision, and positive screens were sent for confirmatory analysis at the laboratory using Gas Chromatography Tandem Mass Spectrometry. BUP levels were detected and quantified by Liquid Chromatography Tandem Mass Spectrometry (Schimadzu Scientific Instruments) with a Raptor C18 analytical column (Restek Corporation; 9304A12).

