#### 2.6.3. Interventions for Experimental Group

In week one of outpatient care, participants allocated to the BUP/NX-F and TDM (experimental) group will receive directly supervised doses according to their dosing schedule. Participants are required to randomly provide a minimum of three negative UDS during these visits on a random basis. If the participant is able to meet this this requirement, a CM protocol will enable them to receive a one-week prescription of medication for self-administration at home. On return for their prescription to be refilled, a negative UDS will enable the participant to receive a two-week prescription and then a three-week prescription. On the other hand, if the participant is not able to meet the initial requirement (i.e., they fail to attend all appointments or provide at least three negative UDS) they will receive supervised dosing for another week (five days for daily dosing schedule and two days of take home for the weekend). At any point, a positive UDS will either hold the participants on five-day supervised dosing or step them down to this arrangement from the two-week or three-week dosing arrangement.

For the TDM element, after the participant has been able to earn a two-week take-home prescription, a blood sample will be collected during a clinic visit for laboratory to measurement of BUP level labelled the “observed concentration”. On the sample collection day, participants will be strictly advised not to take their BUP/NX-F dose and the quantity of medication dispensed will be accounted for by the pharmacy. The exact time of blood sample collection, the time of the last BUP/NX-F dose taken/administered, and the established BUP EL.R will be applied in the function of first order kinetics (Figure S1) to predict the participant's concentration labelled as “predicted concentration” of BUP. If the observed and predicted concentration values do not differ by more than 15%, the participant will be classified “adherent”. Participants who are adherent will be stepped up to a three-week take-home prescription. All nonadherent participants will be stepped down to a one-week take-home prescription.

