On a random basis, all participants who attain the three-week take-home prescription will be invited to visit the clinic between scheduled visits to give a blood sample for BUP testing and also to take a UDS. Nonadherent or nonabstinent participants will be stepped down to two-week take-home prescription while adherent and abstinent participants will receive a four-week take-home prescription at the next scheduled visit (the maximum permitted for the trial). During outpatient treatment, participants who are assessed as both nonadherent and nonabstinent will be reset to supervised dosing.

During the first week of outpatient care, two medication management foundation sessions will be scheduled to help participants (1) understand the importance of taking BUP/NX-F as prescribed, (2) become aware of BUP/NX-F mechanism of action and ways to monitor withdrawal signs and adverse events, (3) recognise and cope with cravings, and (4) build and sustain motivation for abstinence. Then, medication management maintenance sessions will be offered in response to the following four participant conditions: 

*Abstinent and Adherent*. Discussion is held to reinforce and motivate continued abstinence and medication adherence. Prescription for take-home doses will be extended step-wise to a maximum of four weeks. 

*Abstinent but Nonadherent*. Discussion is held to reinforce and motivate continued abstinence, remind the participants about the value of adherence, identify the source of nonadherence and strategies to improve adherence. A follow-up call on the agreed tasks will be arranged and prescription for take-home doses will be stepped down by one level. 

*Nonabstinent but Adherent*. Discussion is held to reinforce and motivate medication adherence and remind participants about the value of abstinence. The context and triggers for using will be assessed and relapse prevention strategies discussed. Additionally, comorbid conditions and social situations will be evaluated with referral to ancillary services. The prescription for take-home doses will be stepped down by one level. 

*Nonabstinent and Nonadherent*. Functional assessment of relapse/lapse will be performed, with referral to an appropriate service if co-occurring conditions were identified. Engagement of family members and close network will be sought to encourage retention. The participant will be transferred to five-day supervised BUP/NX-F dosing.

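### The primary outcome is a mean percentage of negative urine screens in the Abstract but a raw count in Section 2.7.1, and the count mixes visit frequency with abstinence

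*Protocol article*

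**What the plan says.** The protocol article states two primary outcomes.

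- Abstract, Methods: "The primary outcome is the mean percentage of negative UDS over 16 weeks".
- Section 2.7.1: "The primary outcome measure for the study will be the count of negative opioid UDS (excluding BUP) over 16 weeks". It gives no denominator and adds: "Scheduled appointments for a UDS that are missed will be conservatively imputed as positive for opioids".

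The number of screens per participant is tied to attendance. The heading of Section 2.4.1 reads "Urine Drug Screen (with Confirmatory Testing; Baseline and Every Clinic Visit", and Table 2 has no UDS row, so the article gives no testing calendar common to both arms.

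Attendance differs by arm:

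- Experimental arm (Section 2.6.3), week 1: "Participants are required to randomly provide a minimum of three negative UDS during these visits". Success then spaces visits out: "a negative UDS will enable the participant to receive a two-week prescription and then a three-week prescription", and later "adherent and abstinent participants will receive a four-week take-home prescription at the next scheduled visit". A positive screen makes attendance denser again.
- Control arm (Section 2.6.4): dosing is "according to preference of daily, twice weekly, or every two weeks alternatives", with take-home doses contingent on negative UDS. Table 3 caps take-home supply at two weeks here, against four in the experimental arm.

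Section 2.9 plans a fixed-effects logistic model for the primary outcome, a t-test or Mann-Whitney test for group differences, and a sensitivity analysis on observed screens without imputation.

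**The concern.** A count of negative screens is the number of tests multiplied by the share that are negative. With a fixed calendar common to both arms, count and percentage would rank participants alike. Here the number of tests depends on earlier results in one arm and on dosing preference in the other, so the two outcomes can disagree and even point in opposite directions. In the experimental arm, doing well reduces the number of tests and so caps the count.

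Section 4 says that data analysis is in progress. Two stated primary outcomes that can disagree leave room for the choice to be made after results are known.

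**Working it through.** **1. Tests available over 16 weeks.** These are read from the visit rules.

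*Experimental, always negative and adherent.* I assume one step up at each refill, no delay from laboratory turn-around and one random call-in. Refills then fall at the end of about weeks 2, 4, 7, 11 and 15. Total = week-1 screens + 5 refills + 1 call-in:
- 3 in week 1: 3 + 5 + 1 = 9
- 5 in week 1: 5 + 5 + 1 = 11
- 7 in week 1: 7 + 5 + 1 = 13

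*Experimental, held on five-day supervision:* up to 16 × 5 = 80.

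*Control, attending at the preferred dosing frequency:* every two weeks 16/2 = 8; twice weekly 16 × 2 = 32; daily 16 × 5 = 80 or 16 × 7 = 112.

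All the fully abstinent participants score 100% on the percentage. On the count they score 9 to 13, 8, 32, or 80 to 112.

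**2. Break-even.** A twice-weekly control equals the 9 of a fully abstinent stepped-up participant when negative 9/32 = 28% of the time. Someone tested five days a week does so at 9/80 = 11%.

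**3. Expected difference in counts.** Difference = p_E × 9 − p_C × (mean control tests), where p is the share negative. The control mix is an assumption, because the article gives none.

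| Control mix (daily / twice weekly / two-weekly) | Mean tests | Equal, 60% v 60% | Experimental better, 75% v 60% |
|---|---|---|---|
| one third each | 40 | 5.4 − 24.0 = −18.6 | 6.75 − 24.0 = −17.25 |
| 0 / 50% / 50% | 20 | 5.4 − 12.0 = −6.6 | 6.75 − 12.0 = −5.25 |
| 0 / 20% / 80% | 12.8 | 5.4 − 7.68 = −2.28 | 6.75 − 7.68 = −0.93 |
| 0 / 0 / 100% | 8 | 5.4 − 4.8 = +0.6 | 6.75 − 4.8 = +1.95 |

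The first three mixes were also simulated, with 92 per arm and beta-distributed individual rates. With equal abstinence, a t-test on counts wrongly favoured control in 100%, 100% and 91% of runs. With the experimental arm truly better, it still favoured control in 100%, 100% and 18.5%, while the percentage favoured the experimental arm in 98% to 99%.

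**4. Allowing step-downs.** Fixing 9 tests for every experimental participant is a simplification, since participants with positive screens are tested more often. A second simulation applied the stepping rules with identical abstinence in both arms (mean 65% negative, 92 per arm). Mean counts were 11 to 22 in the experimental arm, against 5, 21 or 52 for two-weekly, twice-weekly or daily controls (0.65 × 8, × 32, × 80). The gap runs from 11 − 52 = −41 to 22 − 5 = +17, so its sign is set by the control schedule. The raw participant-level percentage was off by only about 1 to 2 points.

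**5. Fit with the rest of the plan.** Let N be negatives, M missed screens and S scheduled screens.
- Count: N with imputation and N without it. The imputation rule has no effect, and the observed-screens analysis in Section 2.9 repeats the primary one. A complete-case analysis would differ only if it dropped whole participants.
- Percentage: N/S with imputation, N/(S − M) without. Rule and sensitivity analysis both have content.
- A logistic model needs a binary response or negatives out of tests, not an open-ended count.

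**6. The percentage needs a rule after discontinuation.** Take a participant seen five days a week, always negative, who leaves after week 8. If the old schedule keeps running, 8 × 5 = 40 positives are imputed and the score is 40/80 = 50%. If imputation stops at three missed appointments (the discontinuation rule in Section 2.7.2), it is 40/43 = 93%. A participant on a four-week supply would be charged only 8/4 = 2.

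**The case against.** The strongest reply is that the article, read as a whole, intends a proportion. The Abstract says so, and the imputation rule and logistic model make sense only that way. The harm then arises only if the count is really what is compared. This is a fair limit on the consequences, but it does not remove the contradiction. Section 2.7.1 is the defining section, and the t-test or Mann-Whitney test in Section 2.9 could be run on counts.

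Four stronger readings are tempting and are not supported:

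- *The count measures scheduling rather than abstinence, and visit frequency will decide the trial.* The count reflects both. Control frequency is not pure preference either, because take-home doses depend on negative UDS. The control mix is unknown, so the near-100% rejection rates illustrate assumed schedules and do not predict this trial.
- *The imputation distorts the count.* It cannot, since a missed screen adds zero either way. The 40-versus-2 contrast concerns only the percentage, and only if imputation continues after discontinuation, which the article does not say. The 40 also needs five visits a week; a thrice-weekly participant would be charged 8 × 3 = 24.
- *Every positive screen returns the participant to supervised dosing.* Section 2.6.3 says this in one place and elsewhere steps a nonabstinent but adherent participant down one level. Those statements must be reconciled; under either, attendance becomes denser.
- *A fixed-window index must become the primary outcome.* That would be a third outcome, found in neither place, and a design preference. It is not bias-free: with abstinence declining over time (an assumed trend), a first-screen-per-window index moved by up to about 2 points against the experimental arm. The raw percentage moved by up to 5.

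**Conclusion.** The concern holds. The article states two different primary outcomes. The one in Section 2.7.1 is confounded with visit frequency: at complete abstinence it gives about 9 to 13 for a stepped-up experimental participant against about 8, 32 or 80 or more for a control. If counts are compared, a significant or reversed result can arise with equal abstinence. Which arm gains, and by how much, depends on the control visit mix.

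The contradiction, the absence of a common testing calendar and the mismatch with the imputation rule and logistic model come straight from the text. The test counts rest on my reading of the stepping rules and on attendance following the preferred dosing frequency. The simulation results also rest on assumed abstinence rates, assumed control mixes and 92 participants per arm.

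**What to change.** - In Section 2.7.1, replace the count with the participant-level percentage of opioid-negative UDS (excluding BUP): negatives divided by scheduled UDS, with a missed scheduled UDS counted as positive.
- State how scheduled UDS are counted after discontinuation.
- Use the same definition in the Abstract, 2.7.1 and 2.9, and fix it before outcomes are seen by arm. The article does not say whether that point has passed; if it has, the report should say so.
- Because the denominator still varies with schedule, add a sensitivity analysis on a grid common to both arms. One option is one index UDS per four-week window, scored as percent negative out of 4; the longest permitted supply is four weeks. Keep the non-imputed analysis, which has content once there is a denominator.

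The cost is small: wording and derivation work, with no new data. The remaining weakness is a schedule-related bias in the percentage of about 1 to 2 points in simulation, possibly more if abstinence changes over time. The common-grid analysis is there to expose it.

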#### 2.7.2. Secondary Outcome

Retention as defined as completion of the 16-week outpatient treatment without interruption. All participants who miss three consecutive appointments will be judged to have discontinued treatment.

#### 2.7.3. Exploratory Outcomes

There is change in psychosocial functioning from baseline at the end of the 16-week treatment. There is correlation of participant demographics, clinical data, BUP EL.R, and BUP/NX-F maintenance dose with the primary and second outcome.

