## 2. Methods

### 2.1. Study Design, Population, and Setting

The Suboxone Treatment and Recovery Trial (STAR-T) is a single centre, 16-week outpatient intervention, two-arm, pragmatic, phase IV randomised controlled trial of OAT and adjunctive TDM for OUD. The study population is adults (≥ 18 years) with current OUD.

The study setting is the specialist OUD treatment and care programme operated by National Rehabilitation Centre (NRC), Abu Dhabi, United Arab Emirates (UAE; www.nrc.ae). In the UAE, use and combination use of heroin, morphine, and illicit tramadol are the most prevalent [29, 30]. The NRC treatment programme includes an inpatient unit for assessment and management of medical and mental health comorbidities with (poly) substance and alcohol use disorders [29–31]. In 2002, the NRC introduced OAT with BUP with induction and stabilisation procedures conducted in the inpatient unit. However, following concerns about medication diversion in 2011, the NRC suspended all new admissions to OAT pending the development and findings from the present study.

Following a standard of care protocol for OAT, all participants will first complete inpatient care (up to four weeks) to achieve medically supervised withdrawal and stabilisation on BUP/NX-F and to estimate the BUP Elimination Rate (EL.R). After study enrolment and prior to discharge, participants will be randomly allocated (1:1: using an online randomisation service [32] with no stratification) to an experimental group (that immediately received 16 weeks of outpatient BUP/NX-F maintenance, standard case management, and manualised adjunctive medication management with TDM monitoring and CM) or to a treatment-as-usual, control group (that immediately received BUP/NX-F and standard case management and usual medication management only). Using ongoing medication management, TDM, and CM protocol, participants in the experimental group will be able to receive up to four weeks of medication on a take-home basis. All participants will continue to receive ongoing treatment after 16 weeks as usual.

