### 2.3. Participant Eligibility and Enrolment Procedure

The participant inclusion and exclusion criteria for the study are summarised in Table 1. Screening of patients for study eligibility was carried at intake before admission to the inpatient detoxification unit.

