### 2.4. Research Assessments

The following measures were recorded prior to randomisation (baseline), during the outpatient treatment phase (as shown in parentheses; see Table 2 for summary)

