#### 2.4.4. Patient Health Questionnaire (PHQ-9 [37]; See Table 2 for Frequency of Administration)

The PHQ-9 is as a validated, self-administered 9-item scale recording frequency of depression-related symptoms according to the DSM-IV depression criteria using responses over the past two weeks. The PHQ-9 screens for mild, moderate, moderately severe, and severe depression at cut-offs of 5, 10, 15, and 20, respectively. A validated Arabic version downloaded from the PHQ Screeners webpage [www.phqscreeners.com] was used in the present study.

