### 2.10. Analyses for Exploratory Outcome

Bivariate correlation tests to explore correlations with study outcomes will be performed. Specifically, Pearson's correlation will be applied for continuous and Spearman's rho test for categorical data. Factors demonstrating significant correlation and those with potential impact on the primary outcome will be studied for predictive power using a simple linear regression model. Finally, analysing for the effect of confounders will be done using univariate analyses for factors generating higher correlation (>0.5). The mean change from baseline scales or within group change will be analysed using a generalised linear model framework. A paired* t*-test will be conducted where normal distribution is assumed or alternatively Kruskal-Wallis test. The magnitude of change from baseline will be estimated using bias corrected Hedge's* g* effect size. Mean difference between groups will be analysed using student* t*-test where normal distribution is assumed or a Mann-Whitney test.

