## Figures and Tables

**Figure 1 fig1:**
[figure not shown]
Dose assignment and stabilisation.

**Table 1 tab1:** Participant inclusion and exclusion criteria.

*Inclusion criteria*
For a participant to be enrolled into the study he must fulfil all the following inclusion criteria:
(1) Aged 18 and above with no upper limit (usually 64 years);
(2) Current diagnosis of OUD;
(3) Voluntarily seeking OAT treatment;
(3) Resident in the UAE;
(4) Evidence of stable accommodation.

*Exclusion criteria*
Otherwise eligible patients will be excluded from the study for any of the following:
(1) Benzodiazepine use in excess of 20 mg daily diazepam equivalent in the past 28 days;
(2) Known naloxone or BUP hypersensitivity;
(3) Pregnancy;
(4) Hepatic impairment (elevation of liver function tests three times normal);
(5) Suicide attempt in past 12 months;
(6) Involvement in criminal justice system which is likely to result in arrest and incarceration;
(7) Uncontrolled severe mental or physical illness judged to compromise safety;
(8) Mini Mental State Examination score < 17 indicating cognitive dysfunction.

**Table 2 tab2:** Schedule for administering study measures.

Tool/ Screen	Baseline Intake	Inpatient		16 week outpatient study period				
		Detoxification (Daily)	Stabilisation (Weekly)	Week 1 to 4	Week 5 to 8	Week 9 to 12	Week 13 to 16	Week 16 End of study
Eligibility Screen	x							

MCCS	x	x	x	x	x			

Pupil Reflexes	x	x	x	x	x		x	x

COWS	x	x	x	x				

PHQ-9	x			x		x		x

GAD-7	x			x		x		x

BIS-11	x			x				x

PSQI	x		x	x	x	x	x	x

WSAS	x			x				x

PDS	x			x				x

ASI-Lite	x			x				x

MCCS: Minnesota Cocaine Craving (adapted for opioids); PHQ-9: Patient Health Questionnaire; COWS: Clinical Opioid Withdrawal Scale; GAD-7: Generalised Anxiety Disorder; BIS-11: Barrett Impulsiveness Scale; WSAS: Work and Social Adjustability Scale; PDS: Personality Disorder Screen; ASI-Lite: Addiction Severity Index-Lite.

**Table 3 tab3:** Interventions under study groups (TDM; TAU).

Intervention	Randomisation Group	
	TDM	TAU
Induction	Yes	Yes

Stabilisation	Yes	Yes

Baseline assessments	Yes	Yes

Estimating BUP Elimination Rate	Yes	Yes

Medication education	Yes	Yes

Emergency card	Yes	Yes

*Outpatient DOT*	*Yes*	*No*

*Outpatient medication management manualised intervention*	*Yes*	*No*

UDS at outpatient care	Yes	Yes

Providing prescription take-home doses	Contingent on UDS & TDM (i.e., abstinence & adherence)	Contingent on UDS only

*Stepped BUP/NX-F take-home doses*	*Yes*	*No*

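### Within-group change from baseline to week 16 spans the inpatient stay as well as the outpatient phase, because the psychosocial baseline is taken at intake

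*Protocol article*

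**What the plan says.** Section 2.7.3 gives the exploratory outcome as "There is change in psychosocial functioning from baseline at the end of the 16-week treatment". Section 2.10 adds: "The mean change from baseline scales or within group change will be analysed using a generalised linear model framework". It names a paired t-test, or a nonparametric alternative, and bias-corrected Hedges' g for the size of the change. It separately plans a test of the mean difference between groups.

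Section 2.4 places baseline only in general terms: "The following measures were recorded prior to randomisation (baseline), during the outpatient treatment phase". Table 2 is more specific. PHQ-9, GAD-7, WSAS and ASI-Lite each have a single mark ahead of outpatient care, in the column headed "Baseline Intake". That column precedes the detoxification and stabilisation columns. The next mark for each of these scales is in outpatient weeks 1 to 4. PSQI differs, because it also has a mark under weekly stabilisation.

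On the sequence of care, section 2.3 says: "Screening of patients for study eligibility was carried at intake before admission to the inpatient detoxification unit". Section 2.1 then says that "all participants will first complete inpatient care (up to four weeks) to achieve medically supervised withdrawal and stabilisation", with randomisation after enrolment and before discharge.

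**The concern.** The outcome names the end of the 16-week treatment, so a reader will naturally take the within-group change as what happened during those 16 weeks. The starting score, however, comes from before admission. Between that score and the start of the outpatient phase, every participant goes through withdrawal, induction and stabilisation.

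The recall periods widen the gap. PHQ-9 and GAD-7 are completed "using responses over the past two weeks" and ASI-Lite covers the past 30 days, so an intake score describes the period before admission.

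At stake is the interpretation of the paired tests and Hedges' g. Both could show clear improvement even if nothing changed after discharge. WSAS matters a little more than the others, because the Discussion proposes it as a route to estimating change in quality of life.

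**Working it through.** The plan gives no figure on this point, so there is none to reproduce. The check has two parts.

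**1. Timeline from the documents**

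| Step | Source | PHQ-9, GAD-7, WSAS, ASI-Lite | PSQI |
|---|---|---|---|
| Intake, before admission | 2.3, Table 2 | recorded | recorded |
| Inpatient care, up to four weeks | 2.1, Table 2 | not recorded | weekly during stabilisation |
| Randomisation, before discharge | 2.1 | – | – |
| Outpatient weeks 1 to 4 | Table 2 | recorded | recorded |
| Week 16 | Table 2 | recorded | recorded |

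Section 2.6.2 schedules blood samples on days 19 to 24, which suggests that the gap between intake and randomisation is often about three weeks or more. No section resets the baseline after stabilisation. Section 2.4 asks only that baseline precede randomisation, and intake meets that.

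With intake as baseline:

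mean change, intake to week 16 = (inpatient change) + (outpatient change).

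Intake and week 16 alone cannot separate the two terms. In the between-arm difference the inpatient term has the same expectation in both arms, because allocation comes after it, and so it cancels.

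**2. Illustration of size**

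All inputs are assumptions, since the documents give none:

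- 78 participants per arm, which is 92 × 0.85 = 78.2 if the 92 in section 2.8 is read as per arm;
- correlation of 0.5 between intake and week 16;
- no outpatient change and no arm effect;
- 4,000 simulated trials per row.

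| Inpatient recovery (SD) | Mean within-group change (SD) | Paired test, p < 0.05 | Between-arm difference (SD) | Between-arm test, p < 0.05 |
|---|---|---|---|---|
| 0 | 0.00 | 5% | 0.00 | 5% |
| 0.25 | −0.25 | 59% | 0.00 | 5% |
| 0.5 | −0.50 | 99% | 0.00 | 6% |
| 0.8 | −0.80 | 100% | 0.00 | 5% |

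Hand check of the second row: the SD of change is √(2(1 − 0.5)) = 1, its standard error is 1/√78 = 0.113, and 0.25/0.113 = 2.21. A test statistic centred at 2.21 exceeds 1.96 in roughly 60% of trials, which agrees.

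The shift in the mean does not depend on the number of participants; the rejection rates do. With a baseline taken after stabilisation, the expected within-group change in this illustration is zero and the paired test rejects in about 5% of trials.

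**The case against.** The strongest reply is that the plan never claims what is being criticised. A reader might infer that it credits the outpatient treatment with recovery that came earlier. Sections 2.7.3 and 2.10 do not say so: they give a start point, an end point and a measure of change, and plan the between-group test separately. That reply stands. The fault is an outcome whose wording invites a wrong reading, not a stated causal claim.

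A reader might also infer that the second exploratory aim is compromised because its predictors come from the period before admission. The documents do not support this. Section 2.2 speaks of associations between psychosocial functioning and the outcomes, and no section fixes the time point of the predictor. Severity at presentation is a legitimate prognostic factor in any case.

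Third, Table 2 already has a weeks 1 to 4 reading on the affected scales, which separates early from later change even for participants already enrolled. This stands, with two limits: the table does not say which week, and the reading follows randomisation, so it can serve descriptively but not as a baseline for the arm comparison.

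Finally, a baseline late in the ward stay is no clean answer. The two-week recall of PHQ-9 and GAD-7 would then fall within supervised inpatient care, and change from it would include the return to the community. This also stands, and it is why new measurement is only optional below.

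**Conclusion.** The concern holds for the within-group analyses. On PHQ-9, GAD-7, WSAS and ASI-Lite, change from baseline to week 16 is change since before admission, and its paired test and Hedges' g cannot be read as change over the outpatient treatment. The same applies to PSQI if its intake score is used, which the plan leaves open. BIS-11 and PDS follow the same single-intake pattern but measure trait or personality features and are probably less exposed.

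The timing does not bias the randomised comparison, and the primary and secondary outcomes do not use these scales. The affected outcome is exploratory, so the severity is minor.

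The size is unknown. A reader might want a multiplier: if a share f of the total change is inpatient, the mean change is overstated by 1/(1 − f), or 2 times at f = 0.5. That factor carries over to Hedges' g only if the standardising SD is the same under both baselines, and section 2.10 does not say which SD is used. If g uses the SD of change, with assumed correlations of 0.3 from intake and 0.5 from a later baseline, the factor becomes 2 × √(1.0/1.4) = 1.69. Neither f nor the correlations are in the documents, so no such factor should be quoted as an estimate.

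**What to change.** Three changes use data already scheduled:

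1. For PSQI, define baseline as the last weekly stabilisation reading before randomisation, and report the change from intake to that reading separately. This shows the inpatient component for sleep; it cannot be carried over to depression, anxiety or functioning.
2. For the other scales, report within-arm change as change since admission, including inpatient care. Show the weeks 1 to 4 reading descriptively, so that early and later change can be seen apart.
3. State in sections 2.7.3 and 2.10 that conclusions about treatment effect rest only on the between-arm difference at week 16, adjusted for the pre-randomisation score. The generalised linear model framework already named can accommodate this.

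The cost is a few sentences and one or two added table columns. The PSQI within-arm effect may come out smaller.

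Optionally, PHQ-9 and GAD-7 (16 self-rated items) could be repeated shortly before randomisation. This helps only if enrolment continues. Section 4 calls the study ongoing but also says that data analysis is in progress, so few or no participants may remain. The ward-stay recall problem would apply, so such a reading should supplement the intake score, not replace it.
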